### Trial design

3.1

This is a rater-blinded, active-controlled, parallel-group pilot study to assess the efficacy of Sativex associated with robotic-rehabilitation in improving the motor performances of Multiple Sclerosis patients. This study will be conducted at the IRCCS Centro Neurolesi Bonino-Pulejo in Messina, Italy. The study protocol was approved by the Ethical and Research Committee of IRCCS Centro Neurolesi Bonino-Pulejo (13/2016 vers, n 1 23/11/2016). The trial is registered under trial gov. (NCT03186664). The study purpose will be explained to the participants, and patients’ consent will be obtained before the enrollment by the principle investigator.

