### Statistical analysis

3.13

The Wilcoxon signed ranks test on the T0-T1-T2 differences concerning the different clinical outcome measures (EDSS, FIM, MAs, 10mW, 6MW, HSD, MSQOL 54) will be carried out in both groups. The α-level for significance will be set at *P* < 0.05. The Bonferroni correction will be used in multiple comparisons. Data will be expressed as mean or percentage ± standard deviation. The effects of the treatment on RMT, peak-to-peak MEP amplitude, SICI, and ICF will be evaluated in separate repeated-measures analyses of variance (rmANOVA). For each dependent variable, we will compute a 2-way rmANOVA with time (4 levels: T_0_- T_1_-T_2_) and group (2 levels: group A and group B) as within-subject factors. Conditional on a significant F value, post-hoc paired-sample *t* tests were performed to explore the strength of main effects and the patterns of interaction between experimental factors. The Greenhouse-Geisser method will be used if necessary to correct for nonsphericity. All data will be given as means or percent ± standard error. We also will calculate a Fisher Z-transformation concerning the correlations between clinical and electrophysiological parameters.

This is a pilot study. The main aim is to provide evidence which could allow planning of a further confirmatory study. The simple size of 40 patients was determined on the basis of feasibility criteria. Consequently, no formal statistical hypothesis was done

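### The clinical outcomes are tested only within each group, so a pilot meant to inform a confirmatory trial fixes no between-group estimate for them

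*Protocol article*

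**What the plan says.** All references are to the protocol article.

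- **Aim and hypothesis (3.13).** The study is a pilot: "The main aim is to provide evidence which could allow planning of a further confirmatory study". The 40 patients rest on feasibility. "Consequently, no formal statistical hypothesis was done".
- **Decision rule (3.13).** "The α-level for significance will be set at" P < 0.05, and "The Bonferroni correction will be used in multiple comparisons". The number of comparisons is not given.
- **Clinical outcomes (3.13).** "The Wilcoxon signed ranks test on the T0-T1-T2 differences concerning the different clinical outcome measures" (EDSS, FIM, MAS, 10-metre walk, 6-minute walk, Hamilton depression scale, MSQOL-54) "will be carried out in both groups". No other test is named for them.
- **TMS outcomes (3.13).** RMT, MEP amplitude, SICI and ICF each get a two-way repeated-measures ANOVA with time "and group (2 levels: group A and group B) as within-subject factors". Paired t tests follow only if F is significant.
- **Dispersion (3.13).** Mean or percentage with SD is promised after the Wilcoxon tests, then mean or percent with SE after the ANOVA. The second statement covers all data.
- **Purpose elsewhere.** Section 3.1 describes a parallel-group pilot "to assess the efficacy of Sativex associated with robotic-rehabilitation in improving the motor performances". Section 2 asks what Sativex contributes when combined with robotic training.
- **Sample size (3.12).** A minimum of 36 per group, for more than 80% power to detect an interaction, with an effect size of 0.61.

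**The concern.** The question in sections 2 and 3.1 is comparative: both groups receive Lokomat training, and the interest is in what Sativex adds. A signed-rank test asks only whether a group changed from its own baseline. Both groups may change because of the training, the passage of time or regression to the mean, and such a test cannot separate these from a drug effect.

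The temptation will be to compare the two P values and read one significant and one non-significant result as a difference between groups. That inference is invalid, yet it is the only A-versus-B reading that the stated clinical analysis offers.

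The declared aim suffers too. Sizing a confirmatory trial needs a between-group difference on a clinical endpoint with its uncertainty, and the matching SD. The plan fixes a test that gives neither the difference nor its interval, and describes the SD ambiguously.

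**Working it through.** **1. The plan's own figure.** Inputs from 3.12: effect size 0.61 (metric not stated), power above 80%, 36 per group. Two-sided alpha 0.05 is assumed.

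- Read as a standardised difference between two means: n = 2 × (1.96 + 0.842)² / 0.61² = 42.2, so 43 per group (44 with the t distribution). With 36 per group, power is 72 to 74%. One-sided, n = 33.2, so 34.
- Read as Cohen's f for a group-by-time interaction (2 groups, 3 or 4 times, assumed correlation 0 to 0.7): 5 to 11 patients in total.

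The 36 is not reproduced under the stated design. For this point it matters more that 3.12 sets a powered target for an interaction, while 3.13 denies any formal hypothesis and plans 40 patients, not 72. In 3.13 the interaction analysis is given to the TMS measures only.

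**2. What each planned analysis estimates.**

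| Outcomes | Planned method | A-versus-B quantity? |
|---|---|---|
| Seven clinical scales and walking tests | Signed-rank test within each group | None |
| RMT, MEP, SICI, ICF | Group × time ANOVA | Yes, as an F test |

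**3. How misleading two within-group tests can be.** Assume both groups truly improve by the same amount, d SD of change, so the group difference is zero. Use a paired t test (n = 20, two-sided 0.05) as a stand-in for the signed-rank test. If each group's power is p, the chance that exactly one group is significant is 2p(1 − p).

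- d = 0.30: p = 0.247, 2 × 0.247 × 0.753 = 37%
- d = 0.45: p = 0.480, 2 × 0.480 × 0.520 = 50%
- d = 0.61: p = 0.735, 2 × 0.735 × 0.265 = 39%

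Bonferroni does not cure this. At 0.05/7 (seven is an assumption) and d = 0.45, p = 0.194 and the chance is 2 × 0.194 × 0.806 = 31%.

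**4. What an estimate would give at the actual size.** The 95% CI half-width for a difference in mean change, in units of the SD of change, is t(0.975, 38) × √(2/20) = 2.024 × 0.316 = 0.64. At 36 per group it would be 1.994 × √(2/36) = 0.47.

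**5. Why the SD must be labelled.** With equal SDs at two visits and correlation ρ (assumed), SD of change = SD of levels × √(2(1 − ρ)). The multiplier is 1.18, 1.00, 0.77 and 0.63 for ρ = 0.3, 0.5, 0.7 and 0.8. Sample size scales with its square: 1.4, 1.0, 0.6 and 0.4. Mistaking one SD for the other could therefore change a later sample size materially. SD and SE are interconvertible (at n = 20, SD = SE × √20 = 4.47 × SE), but only if the reader knows which is shown.

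**The case against.** The strongest reply is that this is a condensed article. Confidence intervals, SDs of change and visit correlations are details that a full protocol or SAP commonly holds, and the investigators will have the raw data in any case. That stands: the absence of a CI alone is no finding. It does not rescue the clinical analysis, because the article names the test, the alpha level and the correction, and the named test answers a different question from the one in sections 2 and 3.1.

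A reader might also infer more than the text supports:

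- **That the plan cannot yield the SD of change.** Not established. Section 3.13 does not say that the SD is given visit by visit. The statement comes shortly after the tests on differences and may refer to them. For the TMS measures, the ANOVA error term also carries this information under sphericity. Only the ambiguity is demonstrable.
- **That no group comparison is planned at all.** Wrong for the TMS outcomes, although group is mislabelled there as a within-subject factor.
- **That the later trial will be sized from significant, hence inflated, effects.** No section sets a progression or sizing rule. Only the post-hoc t tests depend on a significant F.
- **That 3.1 flatly contradicts 3.13.** The same sentence in 3.1 calls the study a pilot, so the two differ in emphasis. The direct conflict is between 3.12 and 3.13.

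Finally, the 0.64 SD describes a two-sample contrast that the plan does not contain for clinical outcomes. It is the precision of the proposed analysis, not a property of the planned one.

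**Conclusion.** The point holds for the clinical outcomes. As fixed in 3.13, their analysis gives no between-group effect, so it can neither assess what Sativex adds nor supply the estimate the declared planning aim calls for. The SD/SE wording is unclear and inconsistent, and 3.12 conflicts with 3.13 on hypothesis and sample size.

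On size: if both groups improve equally by 0.30 to 0.61 SD of change, two within-group tests at 0.05 would disagree in 37 to 50% of trials (paired-t approximation). A between-group estimate would have a 95% half-width of about 0.64 SD of change with 20 per group and no dropout. That is wide, but open about what the pilot can say. The normal-theory figure is only a guide for ordinal scales such as EDSS and MAS.

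One limit remains. Under 3.4, group A holds only patients who responded to Sativex in the first month, so even a correct A-minus-B difference is not a clean randomised effect. This should be changed, at little cost.

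**What to change.** In 3.13:

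1. For each clinical outcome, make the A-minus-B difference in change (T0 to T1, T0 to T2) with its 95% CI the main result. Within-group changes may stay as description.
2. State that the SD reported is the SD of change per group, and remove the conflict between SD and SE.
3. Label all P values exploratory.
4. Say beside the estimate that group A is restricted to responders (3.4), so that it is not carried into planning as a randomised treatment effect.

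Across sections: reconcile 3.1, 3.12 and 3.13. Either the 36-per-group calculation and its interaction hypothesis stand, or the study is a feasibility-sized pilot of 40 without a formal hypothesis. Section 3.1 should then describe its purpose in matching terms.

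Cost: wording and analysis only, using data already collected. The downside is that the pilot gives up a significance claim.

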## Discussion

4

Spasticity is frequently experienced by individuals with MS, negatively affecting patient's functional outcomes.^[2]^ A previous study showed that Sativex is an effective add on option for moderate to severe spasticity in MS patients resistant to existing therapies, as demonstrated by its capability to improve spasticity and been evaluated by Visual Analog Scale and MAS scores.^[10]^ Sativex could be effective thanks to a double effect on intracortical and spinal plasticity modulating the balance between excitatory and inhibitory neurotransmitters.^[3]^ Cannabinoid receptors may modulate both excitatory transmission and inhibitory transmission at central synapses and have been heavily implicated in multiple forms of synaptic plasticity, such LTP and LTD.^[11]^ The RAGT offers many advantages in terms of patient safety, reduced fear of falling, number of steps practiced (intensity of the training), repeatability, and motor paradigm-induced fatigue as compared with the traditional over-ground training and/or treadmill with or without BWS in MS patients.^[12]^ Moreover, Lokomat optimizes sensory inputs that are relevant to step training, repeated practice, and neuroplasticity. A recent study showed that Lokomat training is effective in reducing reflex and intrinsic stiffness (which abnormally increase in spinal cord injury) and improving the abnormal modulation of reflexes over the ankle range-of-motion.^[13]^ There is growing evidence that the association between RAGT and specific antispastic therapy (as Tizanidine) is effective in improving training speed in people with spinal cord injury as compared to Lokomat alone.^[14]^

Keeping in mind all of these factors, a randomized trial was planned among MS patients that experienced spasticity and gait disturbance to investigate the role of Sativex in boosting the Lokomat effect. In relation to the capability of Sativex in modulating cortical plasticity,^[3]^ we can hypothesize that it can improve functional outcome and strengthen RAGT in effectively improving gait, balance.

## Ethics and dissemination

5

### Ethical requirements

5.1

The Principal Investigator (PI) will conduct the study according to the current version of Declaration of Helsinki, the Good Clinical Practice guidelines, and the local regulations.

### Ethics committee

5.2

The PI will obtain ethics committee approval of the protocol, informed consent form, and other required study documents before starting the study. After approval, the informed consent will not be altered without the agreement of the relevant ethics committee. It is the responsibility of the PI to ensure that all aspects of institutional review are conducted in accordance with current governmental regulations. Protocol amendments will be subject to the same requirements as the original protocol. A progress report will be submitted to the ethics committee at required intervals and not less than annually. At the completion or termination of the study, the PI will submit a close-out letter to the ethics committee.

### Subject information and consent

5.3

A written informed consent will be obtained from all study participants, according to local regulations. The Investigator will inform the subject that participation to the study is voluntary and that refusal will not lead to loss of any benefit or prejudice the relationship with the physician in any way. Before enrolment into the study, each subject will receive a full explanation of the nature and purpose of the study from the Investigator. A clear Information Sheet covering all important aspects in writing will be given to the subject who will read it and have the opportunity to ask any questions whatsoever. The subject will be given adequate time for consideration before he/she is requested to sign the informed consent in duplicate. One of the original copies of the signed informed consent form will be kept by the Investigator.

### Subject confidentiality and data protection

5.4

Before any testing under this protocol, the subjects will also provide all authorizations required by local law (D.Lgs. 196/2003). In agreement with the GCPs, each subject will be identified by a code in an unequivocal manner, which will be the identifier of the subject for the duration of the study.

### Study time table and duation

5.5

Projected first patient in: December 2016Projected number of patients: 40 MS patientsProjected last patient visit: December 2017

12 month-duration
